## Abstract

**Background:**

Health personnel are susceptible to high levels of work stress and burnout due to the psychological and emotional demands of their work, as well as to other aspects related to the organisation of that work. This paper describes the rationale and design of the MINDUUDD study, the aim of which is to evaluate the effectiveness of a mindfulness and self-compassion 4-session programme versus the standard 8-session programme to reduce work stress and burnout in Family and Community Medicine and Nursing tutors and residents.

**Methods:**

The MINDUDD study is a multicentre cluster randomised controlled trial with three parallel arms. Six Teaching Units will be randomised to one of the three study groups: 1) Experimental Group-8 (EG8); 2) Experimental Group-4 (EG4) Control group (CG). At least 132 subjects will participate (66 tutors/66 residents), 44 in the EG8, 44 in the EG4, and 44 in the CG. Interventions will be based on the Mindfulness-Based Stress Reduction (MBSR) program, including some self-compassion practices of the Mindful Self-Compassion (MSC) programme. The EG8 intervention will be implemented during 8 weekly face-to-face sessions of 2.5 h each, while the EG4 intervention will consist of 4 sessions of 2.5 h each. The participants will have to practice at home for 30 min/day in the EG8 and 15 min/day in the EG4. The Five Facet Mindfulness Questionnaire (FFMQ), Self-Compassion Scale (SCS), Perceived Stress Questionnaire (PSQ), Maslach Burnout Inventory (MBI), Jefferson Scale of Physician Empathy (JSPE), and Goldberg Anxiety-Depression Scale (GADS) will be administered. Measurements will be taken at baseline, at the end of the programs, and at three months after completion. The effect of the interventions will be evaluated by bivariate and multivariate analyses (Multiple Linear Regression).

**Discussion:**

If the abbreviated mindfulness programme is at least as effective as the standard program, its incorporation into the curriculum and training plans will be easier and more appropriate. It will also be more easily applied and accepted by primary care professionals because of the reduced resources and means required for its implementation, and it may also extend beyond care settings to academic and teaching environments as well.

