The most well-known mindfulness training program, the MBSR [8–10], consists of 8 weekly sessions lasting 120–150 min, which requires a high level of student commitment to adhere to the sessions and to devote 45 min of daily practice at home. Several attempts have been made to shorten the programs, mostly proposing to reduce interventions to four weeks to make them more viable and accessible while trying to maintain their therapeutic effects and effectiveness and adapting them to the specific target populations and contexts [26–29]. We have found no systematic reviews on the efficacy of these shorter interventions compared to the standard MBSR-based programmes when applied to health professionals—both to attending physicians and to those in postgraduate training. A recently published study [30] concluded that both programmes work in the same way, although the recruited population only included university students. Therefore, it is necessary to undertake studies providing us with greater and more robust evidence on the effectiveness of the abbreviated mindfulness and self-compassion programmes in the group of AP professionals, which will allow us to recommend the inclusion of such programmes in the postgraduate curriculum and in continuing education programmes.

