## Objective

The objective of the MINDUUDD study is to evaluate the effect of a mindfulness and self-compassion training programme on the levels of work stress and burnout in residents and tutors of Family and Community Medicine and Nursing. This study is based on the hypothesis that an abbreviated 4-session programme of mindfulness and self-compassion is at least as effective as the standard 8-session programme to increase mindfulness and reduce the levels of work stress and burnout of AP residents and tutors.

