### Intervention scheme

The interventions will be based on the MBSR programme [8–10] designed by Jon Kabat-Zinn and used at the Medical Center of the University of Massachusetts. Certain self-compassion practices of the Mindful Self-Compassion (MSC) programme [17–19] (Table 1) will be incorporated. The programmes to be tested will be adapted to the participating health care group and will differ by their duration and time dedicated to the tasks [30]:Standard program: The format will be 8 weekly sessions of 2.5 h each. Participants must practice at home for 30 min a day.Abbreviated program: The format will be 4 weekly sessions of 2.5 h each. Participants must practice at home for 15 min a day.

**Table 1 Tab1:** Mindfulness and self-compassion training programs

	8-WEEK PROGRAM	4-WEEK PROGRAM
PRESENTATION BASELINE MEASUREMENT	General explanation, objectives, schedule. Pre-intervention measurements: general data, FFMQ, SCS, PSQ, MBI-GS, JSPE, GADS, AES questionnaires.	
1st SESSION	Raisin exercise. What is mindfulness? Practice: body scan. Informal practice: brushing.teeth Task: 30′ body scan.	Raisin exercise. What is mindfulness? Managing thoughts and emotions during practice. Practice: body scan. Informal practice: brushing.teeth Task: 30′ body scan.
2nd SESSION	Concepts: stress and burnout Practice: mindful breathing (sitting). 3-min mindfulness practice. Informal practice: mindful shower, 3′. Task: 30′ body scan + 10′ sitting.	Concepts: stress and burnout. Primary and secondary suffering. Practice: mindful breathing (sitting). 3-min mindfulness practice. Informal practice: mindful shower, 3′. Task: 30′ body scan + 10′ sitting.
3rd SESSION	Posture. Being versus doing. Managing thoughts and emotions during practice. Practice: yoga (standing meditation). Informal practice: washing the dishes, 3′. Task: alternating body scan or yoga + 15′ sitting.	Unconditional love (metta). Compassion. Practice: conscious movements. Metta for oneself and for others. Informal practice: washing the dishes, 3′, thank you letter. Task: alternating body scan or yoga + 15′ sitting.

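### The hypothesis and the conclusions resting on it require only that the 4-session programme match the 8-session one; benefit over the control group is not a condition, so two ineffective programmes would confirm it

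*Protocol article*

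**What the plan says.** **Hypothesis and conclusion.** The Objective states the hypothesis that "an abbreviated 4-session programme of mindfulness and self-compassion is at least as effective as the standard 8-session programme" in increasing mindfulness and reducing work stress and burnout. The abstract's Discussion carries this into practice: "If the abbreviated mindfulness programme is at least as effective as the standard program, its incorporation into the curriculum and training plans will be easier". The main Discussion says that the results can be applied at once and that tutors and residents will benefit if the hypothesis is confirmed. Study design labels the trial non-inferiority.

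**Control arm.** The Intervention scheme includes a control group without intervention. Sample size is set on a difference of 15 FFMQ points between each experimental group and CG. The main Discussion names both the standard programme and control as comparators. Under Study design and the Intervention scheme, CG is assessed at baseline and once more at 8 weeks. Data collection reconvenes only EG4 and EG8 at three months.

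**The reference programme.** The Background says that MBSR "consists of 8 weekly sessions lasting 120–150 min" and asks participants to "devote 45 min of daily practice at home". The Intervention scheme says: "Standard program: The format will be 8 weekly sessions of 2.5 h each. Participants must practice at home for 30 min a day". The same section states that the programmes are based on MBSR, include self-compassion practices and are adapted to this staff group. Table 1 lists EG8 home tasks that include 30 + 10 minutes (session 2) and 45 minutes (session 7).

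**The concern.** A finding that two active programmes are alike can arise because both work or because neither does. Only the control group can tell these apart, and the hypothesis as worded does not refer to it. A positive answer to the stated hypothesis is therefore compatible with a 4-session programme that does nothing. The article nevertheless makes that answer the ground for curriculum use. The gap remains whatever non-inferiority margin is chosen.

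A lesser matter is what the claim is made against. The reference is called standard, but its home practice is described in three ways that do not agree.

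**Working it through.** **1. The plan's own figure.** Inputs from Sample size: difference 15, SD 20, two-sided alpha 0.05, power 0.80, loss 25%.

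- n per group = 2 × (1.96 + 0.84)² × 20² / 15² = 27.9, so 28.
- With loss: 28 / 0.75 = 37.3, so 38. This reproduces the stated 38.
- Design effect = 1 + (15 − 1) × 0.05 = 1.7, as stated.

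The sizing is for each programme against CG, so the contrast missing from the hypothesis is the one that the trial was sized for.

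**2. How often two ineffective programmes would pass.** Planned size is 44 per arm.

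- SE of an arm difference = 20 × √(2 × 1.7 / 44) = 5.56 points.
- The article gives no margin M, so a range is assumed. With true difference 0 and a one-sided 2.5% test, P(pass) = Φ(M / SE − 1.96).

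| Assumed margin (FFMQ points) | M / SE − 1.96 | P(pass), both programmes ineffective |
|---|---|---|
| 5 | −1.06 | 14% |
| 7.5 | −0.61 | 27% |
| 10 | −0.16 | 44% |
| 15 | 0.74 | 77% |

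Statistical methods names only conventional difference tests at p < 0.05. If matching were read as no significant difference (an assumption; the article does not say so), two ineffective programmes would pass 95% of the time. An EG4 with no effect would pass 56% of the time if EG8 truly gained 10 points, and 23% if it gained 15.

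**3. What a control condition does.** If EG4 must also be superior to CG at two-sided 0.05, an EG4 with no effect passes at most 2.5% of the time, whatever the margin.

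Requiring only EG8 to beat CG is not enough. If EG8 truly gains 5 points and EG4 none, the EG4-EG8 non-inferiority test alone passes with probability Φ((M − 5) / 5.56 − 1.96): 14% for M = 10 and 44% for M = 15. The condition has to fall on EG4 itself.

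**4. What the condition costs in power.** Power for a true 15-point EG4-CG difference = Φ(15 / SE − 1.96).

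- 44 per arm: SE 5.56, power 77%.
- 33 per arm (44 × 0.75): SE = 20 × √(2 × 1.7 / 33) = 6.42, power 65%.
- With the planned 22 per teaching unit, the design effect is 1 + 21 × 0.05 = 2.05, and power is 69% and 57%.

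**5. Home practice in the reference arm.**

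- Background 45 against Intervention scheme 30 min/day: (45 − 30) / 45 = 33% less.
- Table 1, session 2: 30 + 10 = 40 min, (45 − 40) / 45 = 11% less.
- Table 1, session 7: 45 min, no shortfall.

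The gap runs from 0 to one third, depending on the place read. Session time is not reduced: 2.5 h is 150 min, within the 120 to 150 min in the Background. The EG4 column has the same kind of conflict: tasks of 30 and 30 + 10 minutes against 15 min/day in the text.

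**The case against.** The strongest reply is that the control comparison is already planned. The trial is sized on it, the main Discussion names control as a comparator, and Statistical methods compares pre-post differences between the groups. The abstract sentence is a remark about ease of uptake, with no test or threshold attached. Calling a programme at least as effective ordinarily presupposes an effect, and the hypothesis does refer to increasing mindfulness and reducing stress and burnout. A formal testing order may sit in a full protocol or analysis plan that is not shown.

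Much of this stands. A reader might infer that an ineffective short programme would go unnoticed and be recommended. The documents do not support that: an EG4 with no effect should be visible in the EG4-CG results. What remains is that the hypothesis, and both statements resting application on it, are worded in this article without that condition.

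A reader might also infer that the reference arm was weakened by a third and that this tilts the trial towards a finding of equal effect. That is not supported either. The adaptation is disclosed, session time is unchanged, the size of the gap depends on which place is read, and EG4 home practice is also set low. No figure in the documents shows that less home practice narrows the EG4-EG8 difference.

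**Conclusion.** The concern holds as a gap in the stated hypothesis and conclusion, not as a missing comparison. As worded, two equally ineffective programmes confirm the hypothesis. A non-inferiority test would pass them 14% to 77% of the time for margins of 5 to 15 points; adding EG4 superiority over CG limits this to 2.5%.

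These figures rest on SD 20, 44 per arm, design effect 1.7, assumed margins and a normal approximation. With only two teaching units per arm that approximation is optimistic, so real power would be lower, and the 2.5% limit assumes an analysis that holds its level under clustering. The control condition can be checked only post-intervention, because CG has no three-month measurement.

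The home-practice point is secondary: an inconsistency in how the reference is described, with no shown direction of bias.

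**What to change.** 1. In the Objective and in both Discussion statements, say that a conclusion in favour of the 4-session programme requires EG4 superior to CG on FFMQ post-intervention **and** EG4 at least as effective as EG8.
2. State that the EG4-EG8 comparison is uninformative if EG8 is not superior to CG.
3. State that the control condition applies post-intervention only. At that point EG4 is measured at 4 weeks and CG at 8 weeks after baseline, which should be acknowledged beside the result.
4. Reconcile the home-practice figures in the Background, the Intervention scheme and Table 1. This review takes no view on which is right. Word the claim against the adapted 8-session programme used in this trial.

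**Cost.** Wording only; the arm and the contrasts already exist. Since all conditions must be met, this conclusion needs no further alpha adjustment. The price is a narrower claim and an extra condition that a programme truly worth 15 points would fail about 23% of the time at 44 per arm, and about 35% after 25% loss (design effect 1.7).

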**Trial registration:**

The study has been registered at ClinicalTrials.gov (NCT03629457; date of registration: 13.08.2018).

**Electronic supplementary material:**

The online version of this article (10.1186/s12875-019-0913-z) contains supplementary material, which is available to authorized users.

## Background

Work stress and burnout are two common problems among the health personnel of the Spanish National Health System *(Sistema Nacional de Salud-SNS)* due to the high health care burden on this system, among other reasons, with users increasingly demanding solutions to their health problems and needs, insufficient time for training and recycling, and perceived lack of support from managers [1–3]. Many studies show the need to address the physical and psychological consequences of work stress and burnout on health professionals not only by implementing measures regarding work organisation and working conditions but also by providing professionals with tools promoting self-care to help them cope with reality through emotional self-regulation [4, 5].

The Spanish model for training physicians and nurses in different health specialities—known as the *Internal Medical Resident Specialisation Program (MIR)* [6]—is of high quality and is highly regarded in Europe and Latin America. The speciality of Family and Community Medicine (via MIR) is 4 years and that of Family and Community Nursing (via EIR) is 2 years. Both specialities have been developed under the organisation and structure of the Teaching Units (TU) of Family and Community Medicine and Nursing within the SNS. Although residents are expected to assume responsibilities progressively, work stress is inevitable, especially during emergency shifts. An important figure in resident training is the personal tutor. This is a Primary Care (AP) professional with a minimum of five years of experience in patient care who voluntarily and selflessly tutors residents in training. This overload involving patient care and resident supervision generates more work stress and burnout.

Mindfulness is considered a third-generation therapy [7], having attained a strong reputation in the last several decades in Western countries, especially following the development of the MBSR technique by Jon Kabat-Zinn at the University of Massachusetts (USA) [8–10].

Since 2016, in countries such as the USA, at least 30% of medical schools have already included mindfulness in their curriculum plans [7], but in Spain, programmes to reduce work stress and burnout—both in undergraduate and postgraduate studies and in health care settings—by encouraging this practice are still rare. A study conducted by our group found that few AP professionals know of and practice mindfulness [11], even though authors are increasingly recommending training interventions in this technique [12]. Several studies show that by enhancing self-awareness, the professional improves self-care, which improves psychological well-being. Mindfulness-based interventions show good results in improving coping with stress and burnout and in increasing empathy in professionals [13–15], including those dedicated to health care [16].

The term compassion refers to “a feeling of affection or closeness towards other human beings who are suffering” [17–19], an aspect of vital importance in patient care. A key element of compassion for health professionals is self-compassion. If professionals are not accepted and respected, they will hardly display those emotions towards the people to whom they lend their help through empathy [20]. Self-compassion is often linked to mindfulness and is usually incorporated into training programmes [21] because it has been shown to facilitate doctor-patient communication and to improve clinical and psychological patient parameters [22, 23].

Few previous studies allow us to assess the effect of mindfulness programmes and self-compassion therapy in reducing stress and burnout in AP health personnel. The existing studies [16, 24, 25], together with a systematic review of 8 studies including health professionals and teachers, show the favourable effect of these programmes and strong evidence of the use of mindfulness practice to reduce burnout.

The most well-known mindfulness training program, the MBSR [8–10], consists of 8 weekly sessions lasting 120–150 min, which requires a high level of student commitment to adhere to the sessions and to devote 45 min of daily practice at home. Several attempts have been made to shorten the programs, mostly proposing to reduce interventions to four weeks to make them more viable and accessible while trying to maintain their therapeutic effects and effectiveness and adapting them to the specific target populations and contexts [26–29]. We have found no systematic reviews on the efficacy of these shorter interventions compared to the standard MBSR-based programmes when applied to health professionals—both to attending physicians and to those in postgraduate training. A recently published study [30] concluded that both programmes work in the same way, although the recruited population only included university students. Therefore, it is necessary to undertake studies providing us with greater and more robust evidence on the effectiveness of the abbreviated mindfulness and self-compassion programmes in the group of AP professionals, which will allow us to recommend the inclusion of such programmes in the postgraduate curriculum and in continuing education programmes.

## Objective

The objective of the MINDUUDD study is to evaluate the effect of a mindfulness and self-compassion training programme on the levels of work stress and burnout in residents and tutors of Family and Community Medicine and Nursing. This study is based on the hypothesis that an abbreviated 4-session programme of mindfulness and self-compassion is at least as effective as the standard 8-session programme to increase mindfulness and reduce the levels of work stress and burnout of AP residents and tutors.

## Methods/design

### Study design (Fig. 1)

The MINDUUDD study comprises an open-label, pragmatic, non-inferiority, multicentre, cluster randomised controlled trial with three parallel arms. The participating UUDDs will be randomised to one of the three study groups. Interventions will last for 8 weeks for one group (EG8) and 4 weeks (EG4) for the other. In both groups, there will be a follow-up at three months to check the maintenance of the programs’ effect. The control group (CG) will be reassessed 8 weeks after the start of the fieldwork.

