### Sample size

To calculate the sample size, we have drawn on a previous study [25], using as an outcome variable the mean FFMQ score [31]; accepting an alpha risk of 0.05 and a beta risk of 0.2, in a bilateral contrast, 38 subjects are required in each group to detect a difference ≥ 15 points in the FFMQ scale between both experimental groups (EG4 and EG8) and the CG. It is assumed that the common standard deviation is 20. A loss or withdrawal rate of 25% has been estimated [43]. Because this is a cluster randomisation study, we have considered the design effect. The design effect multiplies the sample size by a factor ranging from 1.5 to 3 to achieve the same power, depending on the relationship between intra- and intergroup variance [44]. Estimates of the intra-cluster correlation coefficient (ICC) in randomised clinical trials in AP are generally < 0.05 [45]. This ICC, for a cluster size of 15, results in a design effect corresponding to a factor of 1.7. Assuming this value, the final study sample size would be at least 130 subjects. One hundred and thirty-two (132) professionals will be included, 44 in each comparison group, 22 for each teaching unit.

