### Statistical methods

The descriptive statistics of baseline characteristics of study participants and of questionnaire results—both before and after the intervention—will include means, standard deviations and ranges, medians and interquartile ranges, or frequencies and percentages, according to the variables. The fit of quantitative variables to the normal distribution will be checked by the Kolmogorov-Smirnov test. Prior to testing the effectiveness of the intervention, appropriate statistical tests will be used to examine possible baseline differences between groups (age, sex, time worked, profession, year of residency, previous mindfulness training). A per-protocol analysis will be performed in which all subjects who have completed at least 6 of the 8 sessions in EG8, or 3 of the 4 sessions in EG4, will be considered. All signalment analyses will be intention-to-treat in order to control for non-random dropout effects. Patterns of missing values ​​will be inspected and, if applicable, replaced using appropriate statistical methods.

To compare pre- and post-intervention results, a bivariate analysis will be performed, using Student’s t-test or the Wilcoxon test to compare related samples. Pre-post differences in the results of the questionnaires between the groups will be compared using ANOVA for repeated measures. Finally, a multivariate analysis will verify the effect of the interventions, adjusting for presumably predictive and/or confounding variables. To accomplish this, a multilevel linear regression will be used. The level of statistical significance will be set at *p* < 0.05 for all statistics. The analyses will be performed with SPSS version 17.0 and MLwiN version 3.00 software.

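### The trial is labelled non-inferiority for 4 versus 8 sessions, but it states no margin, is sized for superiority over control and lists only difference tests, so its main hypothesis has no pre-specified criterion

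*Protocol article*

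**What the plan says.** - **Design.** Study design (Fig. 1) calls the trial an "open-label, pragmatic, non-inferiority, multicentre, cluster randomised controlled trial with three parallel arms".
- **Hypothesis.** Objective states that "an abbreviated 4-session programme of mindfulness and self-compassion is at least as effective as the standard 8-session programme" in raising mindfulness and lowering work stress and burnout.
- **Use of the result.** The Discussion paragraph of the Abstract makes easier incorporation into training plans conditional on this: "If the abbreviated mindfulness programme is at least as effective as the standard program".
- **Sample size.** The calculation is made "accepting an alpha risk of 0.05 and a beta risk of 0.2, in a bilateral contrast". It finds that "38 subjects are required in each group to detect a difference" of at least 15 "points in the FFMQ scale between both experimental groups (EG4 and EG8) and the CG", with SD 20 and 25% loss. A design effect of 1.7 follows, and the plan is 44 per arm with 22 per teaching unit.
- **Analysis.** Statistical methods gives paired t or Wilcoxon tests for change within groups, then: "Pre-post differences in the results of the questionnaires between the groups will be compared using ANOVA for repeated measures". A multilevel linear regression adjusts for covariates. Significance is set at p < 0.05 throughout. Intention-to-treat and per-protocol analyses are both planned.
- **Margin.** None is given for any outcome.

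**The concern.** A non-inferiority claim needs three linked items: a margin, a sample size derived from that margin for the comparison in question, and a rule that sets a confidence limit against it. The article declares the design and the hypothesis, but its sample size and its tests answer a different question, namely whether either programme beats no intervention.

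Neither result that the listed tests can deliver settles the hypothesis. Superiority of both programmes over CG does not show that the shorter one is no worse than the longer one. A non-significant EG4–EG8 difference does not show it either, and that result becomes more likely as the trial gets smaller or noisier. At stake is a curriculum recommendation for the short programme that rests on a comparison with no stated standard of success.

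**Working it through.** **1. Reproduce the plan's figure.** Inputs from Sample size: difference 15, SD 20, two-sided alpha 0.05, power 0.80, loss 25%.

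n = 2 × (1.96 + 0.84)² × 20² / 15² = 27.9, so 28 per group; 28 / 0.75 = 37.3, so 38.

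The stated 38 is therefore exactly a superiority calculation. The 15 points are a difference from CG, and nothing in the calculation concerns EG4 against EG8.

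**2. Precision of EG4 minus EG8.** Assumptions: 44 × 0.75 = 33 analysed per arm; 22 × 0.75 = 16.5 per teaching unit; ICC 0.05 (Sample size says generally below this); SD 20 as the residual SD, with no gain from baseline adjustment.

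- Design effect = 1 + (16.5 − 1) × 0.05 = 1.775
- SE = 20 × √(2 × 1.775 / 33) = 6.56
- 95% half-width, normal = 1.96 × 6.56 = 12.9
- 95% half-width, t with 3 df (six units less three arms) = 3.182 × 6.56 = 20.9

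**3. Power to show non-inferiority if the arms are truly equal.** Normal-based power = Φ(M / SE − 1.96). The article gives no margin, so each M below is an assumption.

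| Margin M | M / 6.56 | Power, normal | Power, t with 3 df |
|---|---|---|---|
| 7.5 | 1.14 | 21% | 13% |
| 10 | 1.52 | 33% | 19% |
| 15 | 2.29 | 63% | 36% |

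The smallest margin with 80% power is (1.96 + 0.84) × 6.56 ≈ 18.4 points, more than the whole 15-point effect assumed over control. With the article's own design effect of 1.7 the results hardly move: 21%, 34% and 65%, and a smallest margin of about 18.0.

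**4. Sensitivity to the meaning of SD 20.** The article does not say whether 20 is the SD of raw scores or of change. If it is a raw-score SD and baseline is adjusted for, SE = 6.56 × √(1 − ρ²). With ρ assumed to be 0.5 to 0.7:

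- SE = 5.68 to 4.68 (half-width 1.96 × SE = 11.1 to 9.2)
- normal-based power at margin 10: 42% to 57%
- normal-based power at margin 15: 75% to 89%

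**5. How little a non-significant result would say.** If EG4 were truly 10 points worse, the difference would be non-significant about 67% of the time with SE 6.56, or 58% to 43% with the SEs in step 4. With no allowance for clustering or baseline, SE = 20 × √(2 / 33) = 4.92 and the figure is about 47%.

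**The case against.** Two stronger readings are tempting, and the article supports neither.

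- **That non-inferiority cannot be shown at all.** The planned multilevel regression can give an EG4–EG8 estimate with a confidence interval, and both intention-to-treat and per-protocol analyses, a pairing suited to non-inferiority, are already planned. The estimator exists; the margin and the decision rule do not.
- **That the authors will take a non-significant p-value as proof.** Nowhere does the article say so. What can be said is that it names no other criterion.

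It is also fair to object that this is a condensed article, and that a confidence-limit rule is often left to a fuller protocol or analysis plan. That defence has force for the rule taken alone. It does not reach the sizing. The article sets out a complete sample-size basis, and that basis belongs to a comparison other than the one the declared design rests on. In a non-inferiority trial the margin is an input to that calculation and belongs beside alpha, power and SD.

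Finally, the magnitudes depend on assumptions. Reading SD 20 as a residual SD is the less favourable choice, and the 3-df figures assume a small-sample correction that the article does not specify. This objection stands, which is why ranges are shown. In every variant above, power at a margin of 10 or below stays under 80%.

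**Conclusion.** The concern holds as a mismatch within the article. A trial declared non-inferiority for EG4 against EG8 has no margin, is sized for each programme against CG, and lists difference tests only. Its main hypothesis therefore has no pre-specified criterion, and the comparison that tests it was not sized.

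On the base assumptions (33 analysed per arm, SD 20 without baseline gain, ICC 0.05, normal-based inference), the interval for EG4 minus EG8 spans about ±12.9 points, nearly the full effect assumed over control, and power at a margin of 10 is about one in three. Baseline adjustment could bring a margin of 15 within reach, but a margin that size would allow loss of the entire assumed benefit. Inference that reflects two units per arm would lower every power figure. This should be corrected before data are seen, because it concerns the hypothesis on which the planned recommendation rests.

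**What to change.** **Statistical methods.**
- State that EG4 versus EG8 is judged by the two-sided 95% confidence interval of the baseline- and cluster-adjusted EG4–EG8 difference in FFMQ at one named time point. A time point is needed because the first reassessment falls at 4 weeks in EG4 and 8 weeks in EG8, with another three months after completion.
- Claim non-inferiority only if the lower limit exceeds −M in both the intention-to-treat and per-protocol sets already planned. Fix M before data are seen, clearly below 15 points, and justify it.
- State that a non-significant difference will not be taken to show that the short programme is no worse.
- For work stress and burnout, which the hypothesis also covers, report EG4 versus EG8 as estimation unless margins are fixed for them too.

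**Sample size.** Say that 38 per group refers to superiority over CG, and give the expected half-width of the EG4–EG8 interval with its assumptions.

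**Fallback.** If no defensible margin fits that width, drop the non-inferiority label and present EG4 versus EG8 as estimation.

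**Cost.** Wording in the design, sample size and analysis sections, and no extra participants. Wording alone does not add power: with 44 per arm a defensible margin may well be out of reach, in which case the fallback applies and the claim becomes more modest.
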